## Abstract

**Introduction:**

The persistent development and spread of resistance to antibiotics remain an important public health concern in the UK and globally. About 74% of antibiotics prescribed in England in 2016 was in primary care. The Quality Premium (QP) initiative that rewards Clinical Commissioning Groups (CCGs) financially based on the quality of specific health services commissioned is one of the National Health Service (NHS) England interventions to reduce antimicrobial resistance through reduced prescribing. Emerging evidence suggests a reduction in antibiotic prescribing in primary care practices in the UK following QP initiative. This study aims to investigate the mechanism of impact of this high-cost health-system level intervention on antibiotic prescribing in primary care practices in England.

**Methods and analysis:**

The study will constitute secondary analyses of antibiotic prescribing data for almost all primary care practices in England from the NHS England Antibiotic Quality Premium Monitoring Dashboard and OpenPrescribing covering the period 2013 to 2018. The primary outcome is the number of antibiotic items per Specific Therapeutic group Age-sex Related Prescribing Unit (STAR-PU) prescribed monthly in each practice or CCG. We will first conduct an interrupted time series using ordinary least square regression method to examine whether antibiotic prescribing rate in England has changed over time, and how such changes, if any, are associated with QP implementation. Single and sequential multiple-mediator models using a unified approach for the natural direct and indirect effects will be conducted to investigate the relationship between QP initiative, the potential mediators and antibiotic prescribing rate with adjustment for practice and CCG characteristics.

**Ethics and dissemination:**

This study will use secondary data that are anonymised and obtained from studies that have either undergone ethical review or generated data from routine collection systems. Multiple channels will be used in disseminating the findings from this study to academic and non-academic audiences.

Strengths and limitations of this studyThis study will be the first to evaluate the mechanism of the impact of a financial incentive initiative involving Clinical Commissioning Groups (CCGs) to improve antibiotic prescribing in primary care practices in England.The investigation of multiple mediators in this study will help to identify the contributions of multiple strategies in translating the effects of Quality Premium (QP) while unpacking the extent of the effect of specific mediators.Due to the limited data on practice-level interventions or strategies that might potentially mediate the effect of the QP on antibiotic prescribing, we will not be able to extensively investigate the mechanism of QP impact at the practice level.Nevertheless, extensive investigations will be conducted at CCG level where the QP initiative is implemented and rewards paid out.

## Introduction

The persistent development and spread of resistance to antimicrobials, especially antibiotics, remain an important public health concern in the UK^1^ and globally.^2 3^ Antimicrobial resistance (AMR) is a major threat to the treatment and control of infectious diseases as drug-resistant infections are characterised by prolonged morbidity, increased risk of disabilities, death and cost of healthcare.^4^ A 2014 review estimated that consistent increases in AMR would lead to about 10 million deaths per year by 2050.^5^ Inappropriate prescribing and use of antibiotics in healthcare practices, especially primary care, are integral to the development and spread of resistance.^6 7^

About 74% of the antibiotics prescribed in England in 2016 was in primary care.^8^ The high rate of antibiotic prescribing in primary care has been associated with increased AMR.^9^ While some of the antibiotics prescribed in primary care settings are appropriate, a substantial proportion are cases where antibiotics are not clinically indicated, such as suspected respiratory tract conditions, which can be self-limiting.^9 10^ Uncertainties about diagnosis, (perceived) patient expectations for antibiotics, occupational pressure (eg, consultation rate) and previous experiences are some of the identified drivers of overprescribing in primary care practices.^11–16^

Interventions such as antibiotic stewardship programmes, education and training initiatives targeted at prescribers and patients, financial incentives, among others have been implemented in England to reduce AMR through reduced prescribing. In particular, the Quality Premium (QP) is a National Health Service (NHS) England initiative established in 2013 to reward Clinical Commissioning Groups (CCGs) financially based on the quality of specific health services considered to be of national or local priority and commissioned over a specific period.^17^ Improvement of antibiotic prescribing in primary care was one of the national priorities in the 2015/2016 guidance,^18^ constituting 10% of the premium awarded from 2016/2017 to date.^19 20^ Key aspects of the ‘improved antibiotic prescribing’ priority are reductions in the number of antibiotics prescribed in primary care facilities across England and in the proportion of broad-spectrum antibiotics prescribed in primary care (2015–2017).^19^ Part of the requirements in the 2015/2016 QP guidance for demonstrating improved antibiotic prescribing by CCGs was a reduction in the number of antibiotics prescribed in primary care by 1% of the mean value in England in 2013/2014 (ie, 1.61 items per Specific Therapeutic group Age-sex Related Prescribing Unit (STAR-PU)). This was further increased to 4% in the 2016/2017 guidance.

Emerging evidence suggests a reduction in antibiotic prescribing in primary care practices in the UK following the QP initiative.^21 22^ Prescribing data from England show a reduction of about 2.7 million antibiotic items between 2014/2015 and 2016/2017 financial year.^23^ Eighty-eight per cent of the CCGs in England achieved the target of reducing antibiotic prescribing in the first 2 years of QP.^21^ Also, there has been a significant reduction in the proportion of broad-spectrum antibiotics prescription with 83% of the CCGs meeting their target in the first 2 years.^21^ Such reductions in antibiotic prescribing would be expected to contribute to reductions in the development of resistance.^24^ However, little is known about the mechanisms by which the QP initiative impacted on antibiotic prescribing in primary care practices.

The impact of interventions on specific outcomes is sometimes explained by a series of events. Potential mediators are important in assessing causal relationships like that between QP and antibiotic prescribing in primary care practices in England, where a potential mediator is a variable that hypothetically mediates the effect of QP on the outcome. The conceptual model shown in figure 1 demonstrates the hypothesised pathways for the impact of the QP initiative on antibiotic prescribing and subsequently AMR. The model is developed based on conceptual and empirical evidence from existing literature and the results of qualitative and survey studies conducted as initial stages of the broader STEP-UP (Improving the uptake and SusTainability of Effective interventions to promote Prudent antibiotic Use in Primary care)^25^ project that includes the current study. The conceptual model will be further validated through a stakeholder workshop with key antibiotic stewardship personnel, primary care prescribers and CCG representatives.

**Figure 1 F1:**
[figure not shown]
Conceptual model. The direct effect is represented by the path between the QP initiative (predictor) and antibiotic prescribing rate (outcome). *Not directly observed within our data. AMS, antimicrobial stewardship; CCG, Clinical Commissioning Group; CMO, Chief Medical Officer; QP, Quality Premium; TARGET, Treat Antibiotics Responsibly, Guidance, Education, Tools.

Our conceptual model suggests that in addition to its direct impact, the QP initiative acts by stimulating and enhancing the adoption of existing strategies to reduce and optimise antibiotic prescribing. In investigating the potential pathways connecting QP to reductions in antibiotic prescribing, we will be examining the hypothesis that factors like the Chief Medical Officer’s (CMO) letter, Treat Antibiotics Responsibly, Guidance, Education, Tools (TARGET) toolkit, antibiotic auditing, benchmarking, local incentives at CCG level, prescribers and patients’ antimicrobial stewardship (AMS) education/training can transmit part of the influence of the QP initiative to antibiotic prescribing.

First implemented in September 2014, the CMO letter, which provided social norm feedback to primary care practitioners in England whose antibiotic prescribing rate was in the top 20%, reduced antibiotic prescribing by 3.3% in 6 months in a randomised trial.^26^ The criteria for selecting practices that received the letters in the subsequent years changed with the addition of measures like a change in antibiotic prescribing over time and whether practices have previously been sent CMO letter.

Another important mediator hypothesised in our conceptual model is AMS education/training of prescribers and patients. Educating and training prescribers on the importance of antibiotic stewardship and ways to promote prudence can help prescribers make better decisions on when an antibiotic is indicated and can also improve patients’ knowledge on the appropriate use of antibiotics. AMS interventions targeted at patients can improve their knowledge of when antibiotics are not needed and increase confidence and skills on how to self-care, which can result in reduced consultations for self-limiting illness and thus reduced antibiotic prescriptions.

TARGET is a toolkit developed by the Public Health England (PHE), the Royal College of General Practitioners and other professional societies to promote prudent antibiotic use among prescribers and patients in primary care.^27^ The intervention comprises of multiple resources (patient information leaflets on infection management and antibiotic use, self-assessment checklist for prescribers, antibiotic audit toolkits, interactive workshop presentations, national antibiotic management guidance, training resources and resources for clinical and waiting areas) to provide clinicians and patients with the motivation and skills to use antibiotics prudently.^27^ A qualitative study evaluating prescribers’ attitude and perception about the TARGET toolkit reported that general practitioners described it as useful and important in improving their prescribing behaviours and the expectations of their patients.^28^ The use of resources like the TARGET antibiotics workshop has been shown to reduce antibiotic prescribing rate in a randomised controlled trial.^29^

We hypothesise that the implementation of the QP initiative informed the initiation or wider use of these strategies indicated in the conceptual model as mediators, which will subsequently influence antibiotic prescribing at primary care practices.

The implementation of the QP initiative in NHS England constitutes a natural experiment and offers an opportunity to investigate the preintervention and postintervention periods to understand the mechanism of impact of the QP intervention in reducing antibiotic prescribing rates in primary care practices.^30^ Given the ethical and practical constraints in manipulating exposure in such an intervention, a natural experimental design offers a practical approach to understand the overall effect and mechanism of interventions like QP that offers financial incentives for clinical compliance. The publication of the 2015/2016 QP Guidance^18^ constitutes the ‘intervention’, with periods before this as the ‘control’.

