### Variables

The predictor will be a binary variable indicating the implementation of the QP intervention. The intervention will include all periods after March 2015 when the 2015/2016 QP guidance in England was published, while the control will be periods prior to this. The primary outcome of interest is the rates of antibiotic prescribing at CCG level in England, which will be a continuous variable indicating the number of items (per STAR-PU) prescribed per month.

To account for differences in practice and CCG characteristics that can contribute to variance in antibiotic prescribing, we will be adjusting for the number of general practitioners in each practice (from the NHS Workforce data),^35^ the index of multiple deprivation (from the Department for Communities and Local Government),^36^ prevalence of comorbidities (asthma, chronic obstructive pulmonary disease, diabetes, cancer, chronic kidney disease (from the NHS Quality and Outcomes Framework database)),^37^ the prescribing rate of other non-antibiotic drugs (opioids and benzodiazepines) and seasonal influenza vaccination rate (from PHE).^38^

Mediator variables will be derived from the questionnaire data from a PHE survey,^39^ with 187 of the 209 AMS leads representing CCGs in England and data from other organisations that have evaluated the interventions treated as potential mediators in this study. In the PHE survey, participants were required to complete questionnaire items, which included their adoption of national and local strategies in their respective CCG to enable them to meet QP targets on antibiotic prescribing in primary care. The mediator variables will be binary or continuous variables, indicating the adoption of key interventions and intermediaries that are hypothesised to reflect in the integration of the QP guidance in improving antibiotic prescribing in primary care practices.

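### The CMO letter is listed as a mediator of QP, but its first wave predates QP and letters were assigned on past prescribing, which the listed covariates omit

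*Protocol article*

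**What the plan says.** The Introduction (text after Figure 1) puts the letter first among the hypothesised pathways: "we will be examining the hypothesis that factors like the Chief Medical Officer’s (CMO) letter" and other strategies pass on part of QP's influence. The same section gives its start date, "First implemented in September 2014, the CMO letter, which provided social norm feedback to primary care practitioners in England", and the rule for recipients, "whose antibiotic prescribing rate was in the top 20%, reduced antibiotic prescribing by 3.3% in 6 months in a randomised trial". Later waves changed the criteria "with the addition of measures like a change in antibiotic prescribing over time and whether practices have previously been sent CMO letter".

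The mechanism is worded broadly. The article says that "the QP initiative acts by stimulating and enhancing the adoption of existing strategies to reduce and optimise antibiotic prescribing", and later: "We hypothesise that the implementation of the QP initiative informed the initiation or wider use of these strategies".

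Under Variables, exposure is fixed by date: "The intervention will include all periods after March 2015". The covariate sentence opens with "we will be adjusting for the number of general practitioners in each practice" and goes on to deprivation, comorbidity prevalence, opioid and benzodiazepine prescribing, and influenza vaccination. Prior antibiotic prescribing is not listed. Mediators are to come from a survey of CCG stewardship leads and from other organisations' data, as binary or continuous variables. How the letter will be coded is not stated.

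Under Statistical analysis, each mediation analysis compares one post-QP year with the financial year before QP. Only mediators that show an effect singly go into the sequential model.

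**The concern.** Two separate problems affect the same variable.

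**Timing.** A mediator must be something the exposure can change. Guidance published in March 2015 cannot have caused letters sent in September 2014. Those letters were acting during the control year, so the comparison year already contains part of a strategy that is later assessed as a channel for QP.

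**Assignment.** Receipt depends on past values of the outcome: level of prescribing at first, later also its change and previous receipt. Prescribing persists over time, so places with many lettered practices tend to remain high prescribers. Without prior prescribing in the model, the letter coefficient mixes the letter's effect with the reason the letter was sent.

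Mediation is the study's stated aim, and the single-mediator results decide what enters the sequential model. An error for the letter can therefore carry into the final multiple-mediator analysis.

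**Working it through.** The article states no figure for this point that could be reproduced. The 3.3% is cited from an external trial and is used here only as an input.

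**1. Dates.** From September 2014 to March 2015 is six months. The control year is April 2014 to March 2015. Counting September, the first wave is active in 7 of its 12 months; without September, 6 of 12.

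**2. Effect on the control year.** Inputs from the article: top 20% of practices, 3.3% reduction. Assumptions: every practice weighted equally, the effect constant, and either all or half of the eligible practices lettered.
- All lettered, 7 months: 0.20 × 3.3% × 7/12 = 0.39%
- Half lettered, 7 months: 0.10 × 3.3% × 7/12 = 0.19%
- With 6 months instead: 0.33% and 0.17%

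As a scale only, 0.19% to 0.39% is 19% to 39% of the 1% reduction in the 2015/2016 guidance, and 5% to 10% of the 4% in 2016/2017. Both targets are set against the 2013/2014 mean, not against the control year.

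**3. Strength of selection.** For a normal distribution, the top 20% exceed the rest by φ(0.842)/0.20 + φ(0.842)/0.80 = 1.40 + 0.35 = 1.75 SD on the selection measure. If that gap persisted, a crude comparison would hide a 3.3% reduction once the between-practice coefficient of variation (CV) exceeded 3.3/1.75 = 1.9%.

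**4. Consequence for the indirect effect (illustrative simulation).** From the article: 187 CCGs with survey data, top-20% targeting, true effect −3.3%. Assumed: the mediator is the share of a CCG's practices lettered, 36 practices per CCG, between-practice CV 10% to 30%, 5% to 20% of variance between CCGs, covariates explaining 0 to 90% of CCG-level variance, reliability 0.9. The pooled two-year model has outcome on QP, mediator and covariate, and mediator on QP and covariate; the indirect effect is a × b. The true value is 0.20 × −3.3% = −0.66%.

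| Coding and model | Estimated indirect effect |
|---|---|
| Letter coded 0 in control year, no prior prescribing | +1.1% to +17.8% (wrong sign in all 18 settings) |
| Letter coded alike in both years, no prior prescribing | 0, because a = 0 |
| Letter coded 0 in control year, change score | −0.74% to −1.30%; −1.77% at reliability 0.7 (one setting) |
| Letter coded 0 in control year, adjusted for the CCG's own baseline rate | −0.59% to −0.78% |

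One setting in full (CV 20%, 20% of variance between CCGs, covariates explaining half): a = 0.20, b = +38.0%, so a × b = +7.6%.

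**5. Time series.** Practice data start in August 2013, so there are 20 months up to March 2015: 13 before and 7 from September 2014. If the letter produced a lasting 0.66% drop, fitting a single line through these months tilts the pre-QP slope downward by 0.66 × 45.5/665 = 0.045% per month, about 0.54% per year (half that if half were lettered). Here 665 is the sum of squared centred months and 45.5 is the sum of centred months 14 to 20. That slope is the counterfactual for the post-QP period.

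**6. Existing safeguards.** The dummy-date sensitivity analyses move the start by at most three months, so they reach December 2014 and not September. Regression to the mean is handled only for the high- and low-prescriber subgroups.

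**The case against.** The strongest reply is that the hypothesis never required mediators to begin with QP. The article speaks of enhancing existing strategies and of wider use, and it says letters continued in later years. This stands: later waves can be candidate mediators. It does not rescue the first wave, and the article gives no route by which QP would change who receives a letter.

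Second, the letter's coding is unstated, and a condensed article may leave that to a fuller plan. The survey asks about strategies adopted to meet QP targets, which points to post-QP activity. Figure 1 is not available here, so it cannot be checked whether the letter is marked as not directly observed. This also stands, so the article cannot be said to place the September 2014 letters in the mediator variable.

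Third, a reader might infer that the letter's indirect effect will be reversed in sign. The documents do not support that. The reversal in the simulation depends on an assumed coding and assumed variances. Coded alike in both years, the effect is zero; a change-score model keeps the right sign and exaggerates the size. A yes/no survey item would be a different variable altogether.

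Fourth, the Limitations section concedes reliance on sequential ignorability and likely unmeasured confounding. That caveat is fair but does not settle this point, because prior prescribing is measured: it is the study's own outcome series.

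**Conclusion.** The concern holds in a limited form. The first CMO wave precedes exposure, lies in the control year and cannot transmit a QP effect. Its likely effect on control-year prescribing is small, about 0.2% to 0.4% of the England mean under the assumptions in step 2. Because letters were assigned on past prescribing and the covariate list omits it, the letter's indirect effect is not identified as planned. The bias could run toward zero or to the wrong sign; which one depends on a coding the article does not give.

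Two stronger readings go too far: that the letter cannot mediate QP at all, which the wording on existing strategies and the later waves contradict, and that a sign reversal is established. The practices-per-CCG, variance, covariate and reliability values are all assumptions. The point directly affects one of several candidate mediators, and the sequential model if the letter enters it.

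**What to change.** - Define the letter mediator as letters sent after March 2015, and state its coding and level. Enter receipt in September 2014 as a pre-exposure covariate.
- In the letter model, and in any sequential model that includes it, adjust for prescribing before the control year. August 2013 to March 2014 is already in the dataset. The 2014/15 rate cannot serve, because it is the control-year outcome. Add recent pre-QP change where available. The earlier rate is only a proxy for the measure used to select recipients, so some confounding may remain.
- State that selection in later waves may itself depend on post-QP prescribing, which limits causal reading even after adjustment.
- In the time series, add a September 2014 term as a sensitivity analysis, or state that the pre-QP trend includes the first letter. It should not replace the main model, since it splits 20 pre-QP months into 13 and 7.

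The cost is one recoded variable, a few covariates, some loss of precision and possibly a smaller effect attributed to mediation. The prescribing data needed are already held; letter receipt by wave would have to come from the mediator data sources.

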### Study aim and objectives

Using routinely collected population-level data on antibiotic prescribing in England, this study aims to address the research question: What are the mechanisms and mediators of the impact of a high-cost health-system level intervention, the ‘antibiotic prescribing quality premium’? We will investigate the difference in antibiotic prescribing rate pre-QP and post-QP initiative to establish its direct, indirect (through mediators) and total effects in reducing antibiotic prescribing in primary care practices in England.

